#### Tertiary outcomes

Quality of life, depression, and diet quality will be presented and analyzed as the primary and secondary outcomes. Data from the program adherence and morbidity associated with diabetes will be analyzed using the independent *t*-test. Regarding satisfaction with the program, it will be analyzed descriptively from absolute values and percentages.

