## Abstract

**Background:**

Patient education is a crucial strategy for promoting prevention and diabetes self-management since glycemic control achievement involves taking medications, medical nutrition therapy, physical exercise, and behavior changes. However, patient education programs are still barely implemented in low- and middle-income countries. This trial aims to investigate whether a lifestyle education intervention added to physical exercising is superior to sole physical exercising regarding functional capacity, disease-related knowledge, health behaviors, cardiometabolic health parameters, quality of life, depression, and diet quality in individuals with prediabetes or diabetes.

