**Discussion:**

If superior effectiveness of ExLE compared to Ex program to improve the outcomes measures is found, this program could be delivered broadly in the Brazilian health system, especially in the primary care facilities where most individuals living with prediabetes and diabetes in our country are assisted.

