#### Primary and secondary outcomes

Primary and secondary outcomes will be presented as central tendency and dispersion measures. Data distribution will be analyzed using the Shapiro–Wilk test. The analysis of variance (2 × 2 ANOVA) will compare data between baseline and post-intervention and between groups. An alpha of 5% will be considered for statistical significance, and post hoc comparisons will be performed to detect two-by-two differences. In case of missing data, the statistical procedures will follow the intention to treat.

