## Discussion

To our knowledge, this is the first randomized controlled trial that integrates exercise with patient education, aiming to surpass the benefits of exercise alone for individuals with prediabetes or diabetes in middle-income countries. Our objectives include improving functional capacity, increasing disease-related knowledge, fostering healthier behaviors, optimizing cardiometabolic health parameters, enhancing quality of life, alleviating depression, enhancing diet quality, and reducing diabetes morbidity over 6 months.

This study has the potential to contribute significantly by assessing the effectiveness of a structured patient education program associated with an exercise program that could be applied in the public and private health system in order to improve outcomes related to the prognosis in individuals with diabetes and to prevent type 2 diabetes in individuals with prediabetes. Considering (1) the proven benefits of physical exercise for individuals with diabetes and prediabetes, (2) the role of health education in facilitating better diabetes management and prevention, and (3) its impact on mitigating complications and cardiovascular risk factors, these interventions could substantially improve the quality of life for this population.

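### The superiority question and the roll-out conclusion span the secondary and three tertiary outcomes at the same 5% level, and the outcome tiers carry no inferential consequence

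*Protocol article*

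**What the plan says.** Four places in the protocol article bear on this point.

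- **Aim (Abstract, Background).** The trial is to find out whether the exercise-plus-education arm (ExLE) "is superior to sole physical exercising regarding functional capacity, disease-related knowledge, health behaviors, cardiometabolic health parameters, quality of life, depression, and diet quality". That list covers both primary outcomes, both secondary domains and three tertiary outcomes, without distinction.
- **Test for primary and secondary outcomes (Statistical methods, Primary and secondary outcomes).** All of them get a 2 × 2 ANOVA under one criterion: "An alpha of 5% will be considered for statistical significance, and post hoc comparisons will be performed to detect two-by-two differences".
- **Test for tertiary outcomes (Statistical methods, Tertiary outcomes).** "Quality of life, depression, and diet quality will be presented and analyzed as the primary and secondary outcomes". Two others are handled separately: "Data from the program adherence and morbidity associated with diabetes will be analyzed using the independent *t*-test". Satisfaction is only described.
- **Conclusion (Abstract, Discussion).** The statement on national roll-out reads: "If superior effectiveness of ExLE compared to Ex program to improve the outcomes measures is found, this program could be delivered broadly".

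The outcomes are tiered by name in the Outcomes section, and the sample size is built on walking distance. The Objectives section lists the tertiary outcomes as further matters to be investigated and does not mention superiority there. No section says what a tier means for inference.

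**The concern.** Tiers normally separate what a trial is meant to establish from what only adds support. Here the labels exist, but the aim, the test, the alpha and the conclusion run across them. Three tertiary outcomes are explicitly handled like the primaries.

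At stake is what the trial may conclude. Suppose the shuttle walk distance and the knowledge score show no difference, and one of the remaining outcomes reaches p < 0.05 in favour of ExLE. Nothing in the article stops that result from being presented as superior effectiveness, with the argument for wide delivery attached. The risk that such a result is due to chance is well above what the stated 5% suggests, because there are about a dozen opportunities for it.

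**Working it through.** **Inputs from the protocol article**

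- Secondary outcomes: the eight rows of Table 2, each counted once (health literacy, physical activity, exercise self-efficacy, Mediterranean diet, medication adherence, glycaemic control, anthropometry, cardiac autonomic control).
- Tertiary outcomes named in the superiority aim: quality of life, depression and diet quality, each counted once.
- Total: m = 8 + 3 = 11.
- Alpha: 5% per outcome. The article states one 5% level and no division of it, so the full level for each outcome is the natural reading. The ANOVA F-test is non-directional, so a single test falsely favours ExLE with probability 2.5%.

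**Inputs assumed**

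- ExLE adds nothing on any of the 11 outcomes.
- The test statistics are standard normal with a common correlation ρ. The article gives no correlations, so ρ is varied from 0 to 0.8.

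The article states no family-wise error rate, so there is no figure of its own to reproduce beyond the 5% per test.

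**Independent outcomes (ρ = 0)**

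- At least one false result favouring ExLE: 1 − 0.975^11 = 0.243.
- At least one false result in either direction: 1 − 0.95^11 = 0.431.

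**Correlated outcomes**

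Write each statistic as Z_i = √ρ·U + √(1−ρ)·E_i, with U and the E_i independent standard normal. Then P(max Z_i > 1.96) = 1 − ∫ Φ((1.96 − √ρ·u)/√(1−ρ))^11 φ(u) du. The two-sided version replaces Φ(·) by the probability that Z_i lies within ±1.96 given u.

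| ρ | Favouring ExLE | Either direction |
|---|---|---|
| 0 | 24.3% | 43.1% |
| 0.3 | 19.1% | 37.5% |
| 0.5 | 15.2% | 30.4% |
| 0.7 | 11.2% | 22.3% |
| 0.8 | 9.0% | 18.0% |
| One test | 2.5% | 5.0% |

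The feared error is a false claim for ExLE, so the middle column is the relevant one. Relative to a single test it is 9.0/2.5 = 3.6 times at ρ = 0.8, 15.2/2.5 = 6.1 times at ρ = 0.5, and 24.3/2.5 = 9.7 times at ρ = 0.

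**What the count leaves out**

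- Each secondary row counts once, although Table 2 lists twelve heart rate variability indices in one row and both BMI and waist circumference in another.
- Diet quality counts once, although the Outcomes section defines it through macro- and micronutrient intake.
- Post hoc pairwise comparisons are ignored.
- Diabetes-related morbidity is excluded. It is not in the Abstract's aim, and it gets a t-test for which no alpha is restated. The closing Discussion does list it among the objectives ("enhancing quality of life, alleviating depression, enhancing diet quality, and reducing diabetes morbidity over 6 months"). Including it gives m = 12, with 26% favouring ExLE at ρ = 0 and 16% at ρ = 0.5, so the conclusion does not turn on it.

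**The case against.** The strongest reply is that this is mostly silence. Multiplicity rules for lower-tier outcomes usually stand in an analysis plan, the plan is not at hand, and the article is a condensed text. Silence alone would indeed be no finding. The point rests on what the article does state: a superiority question across three tiers, one shared test and alpha, and a roll-out statement that is not confined to the primaries. If an analysis plan restricts the inference, these sentences still need to be aligned with it.

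Several stronger readings are tempting, and the article does not support them.

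- A reader might infer that superiority is claimed. It is posed as a question, and the roll-out sentence is conditional and hedged.
- A reader might infer that the outcomes have no hierarchy. They are tiered by name, and the Objectives section treats the tertiary ones as additional. What is missing is a consequence for inference.
- A reader might infer that most tertiary outcomes are in the superiority aim. The Abstract names three of six; a fourth appears only if the closing Discussion's list of objectives is counted.
- A reader might infer a decision rule under which one significant tertiary result suffices. No such rule is written. The wording merely permits that use.
- A reader might take the 30% to 43% either-direction rates as the risk of a false claim for ExLE. They also count false results favouring exercise alone, so the directional rates apply.

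**Conclusion.** The concern holds in a limited form. The article asks about superiority on the two primaries, all eight secondary outcomes and three of six tertiary outcomes. It analyses them alike at 5% and leaves the roll-out conclusion open to any of them. If ExLE adds nothing on the 11 lower-tier outcomes, the chance of at least one false result in its favour is about 15% at ρ = 0.5, with a range of 9% (ρ = 0.8) to 24% (ρ = 0), against 2.5% for one test. In either direction it is 30% (18% to 43%).

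These figures rest on an assumed common correlation, on one test per outcome, and on reading the 5% as unadjusted and non-directional. This is a defect in what may be concluded, of moderate weight. It does not bear on how the two primaries are tested against each other.

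**What to change.** In the statistical methods for primary, secondary and tertiary outcomes, state that superiority and the roll-out conclusion rest on the primary outcomes only. State that secondary and tertiary outcomes are reported as supportive estimates with 95% confidence intervals. Reword the Abstract's aim and its closing statement to match.

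A formal procedure for the secondary outcomes, such as Holm or an ordered list tested after primary success, is optional. It is worth adding only if the investigators want a confirmatory secondary claim.

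The cost is a few sentences and no new data. The change should be made before outcome comparisons between the arms are seen; the article gives no database lock date. The downside is that nominally significant lower-tier results can no longer be presented as proof of superiority.

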### Criteria for discontinuing or modifying allocated interventions {11b}

Since study participation is voluntary, participants have the right to withdraw from the study at any time. Upon withdrawal, no further data will be collected from them, although any data previously collected will be preserved in accordance with the terms outlined in the informed consent form. It is important to note that once a participant withdraws from the study, they will not be permitted to re-enter at a later date.

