#### Tertiary outcomes

The tertiary outcomes included in this study will be program adherence, satisfaction with the program, diabetes-related morbidity, quality of life, depression, and diet quality.Program adherence will be measured by the attendance rate in the program for each participant. The attendance rate of participants in the on-site delivery mode will be calculated based on the number of education classes and/or exercise sessions attended, divided by the total number of education classes and/or exercise sessions offered. For participants in the remote delivery mode, the attendance rate will be determined by the number of weeks exercise and /or study diaries were filled out, divided by the program’s duration in weeks.Satisfaction with the program will be measured by questionnaires developed by the researchers. For participants in the on-site delivery mode, the level of satisfaction with the patient education program will be assessed by an 11-item questionnaire, and with the exercise program by a 4-item questionnaire. For participants in the remote delivery mode, the level of satisfaction with the patient education program will be assessed by a ten-item questionnaire and with the exercise program by a five-item questionnaire.Diabetes-related morbidity will be assessed through the number and description of acute complications and diagnoses of chronic complications of diabetes, along with the number of hospitalizations associated with diabetes. The information will be collected using a three-item tool during the 6-month follow-up period.Quality of life will be evaluated using the Medical Outcomes Study 36-Item Short-Form Health Survey (SF-36) [46]. The total scores range from 0 (indicating no quality of life) to 100 (indicating the highest quality of life). This is obtained through a 36-item tool distributed across various physical and mental health domains, including physical functioning, social functioning, role–physical, bodily pain, mental health, role–emotional, vitality, and general health.Depression will be measured by the Brazilian version of the Center for Epidemiological Scale—Depression (CESD) [47]. The total score ranges from 0 (indicating no depressive symptoms) to 60 (indicating the highest level of depressive symptoms). This is obtained through a 20-item tool used to rate how often the interviewed experienced symptoms associated with depression over the past week, such as restless sleep, poor appetite, and feeling lonely. Response options range from 0 to 3 for each item (0 = rarely or none of the time, 1 = some or little of the time, 2 = moderately or much of the time, 3 = most or almost all the time).Diet quality will be measured through the consumption of macro and micronutrients. Food consumption will be assessed using an adapted version of a validated Food Frequency Questionnaire (FFQ) for Brazilian individuals with type 2 diabetes [48, 49], evaluating consumption frequency (daily, weekly, monthly, or yearly), number of portions, and serving size (small, medium, large or extra large). The adaptation of the FFQ was necessary since the individuals in this research have different eating habits than in the validated FFQ study, so regional adaptations were necessary. This adaptation was made based on a food diary on three non-consecutive days, including a weekend day carried out with 65 volunteers with type 1 or type 2 diabetes [42]. The final FFQ consists of 104 food items distributed across eight food groups (“cereals, tubers, roots, and derivatives”; “vegetables and legumes”; “fruits”; “beans”; “meat and eggs”; “milk and dairy products”; “oils and fats”; “sugars and sweets”), as well as 11 items investigating beverages, 4 items investigating oilseeds, and 1 item investigating food supplement.

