### Sample size {14}

The sample size was calculated considering the ISWT distance as the primary outcome, using parameters derived from a previous study involving educational intervention in cardiac rehabilitation [50]. The calculation was performed using R Software version 3.4.3, with the following parameters: a moderate effect size (*d* = 0.20), 80% statistical power, a 5% alpha level, one-sided test, two arms, and three measurements. A total sample size of 200 participants (100 per arm) was determined. Assuming a 20% attrition rate, based on a previous study [50], 120 participants would be enrolled in each arm to ensure that 200 participants complete the study protocol.

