### Plans to promote participant retention and complete follow-up {18b}

There are no plans to promote participant retention. To minimize dropouts on the 6-month follow-up, the participants will receive monthly phone calls to remind them about filling out the diabetes-related morbidity tool and the post-follow-up assessment appointment.

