### Methods in analysis to handle protocol non-adherence and any statistical methods to handle missing data {20c}

The value 0 (zero) will be imputed to replace the missing data in the analysis that will follow the intention-to-treat principle.

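### Diabetes-related morbidity is a raw event count with no observed-time denominator and missing data set to zero, so unobserved follow-up counts as event-free (minor; tertiary outcome)

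*Protocol article*

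**What the plan says.** Five statements in the protocol article bear on this.

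- **Definition** (Outcomes, Tertiary outcomes): "Diabetes-related morbidity will be assessed through the number and description of acute complications and diagnoses of chronic complications of diabetes". Admissions to hospital are a further count in the same definition: "along with the number of hospitalizations associated with diabetes". On the window: "The information will be collected using a three-item tool during the 6-month follow-up period".
- **Test** (Statistical methods, Tertiary outcomes): "Data from the program adherence and morbidity associated with diabetes will be analyzed using the independent *t*-test".
- **Withdrawal** (Criteria for discontinuing or modifying allocated interventions): "Upon withdrawal, no further data will be collected from them, although any data previously collected will be preserved".
- **Missing data** (item 20c): "The value 0 (zero) will be imputed to replace the missing data in the analysis that will follow the intention-to-treat principle". Morbidity is not exempted.
- **Expected loss** (Sample size): "Assuming a 20% attrition rate, based on a previous study [50], 120 participants would be enrolled in each arm". No figure is given by arm.

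On collecting the morbidity tool, the retention section says only that "the participants will receive monthly phone calls to remind them about filling out the diabetes-related morbidity tool". The article mentions no rate, person-time, offset or time-to-event method for this outcome.

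**The concern.** A count of events means something only relative to the time over which events could be recorded. Here that time varies between participants, because collection ends at withdrawal, yet the planned comparison uses the count alone. Zero is also not a neutral fill-in for an event count: it is the best possible result. A participant who leaves is recorded as having had no further events or, if the whole value is missing, none at all.

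Two consequences follow. The level of morbidity is too low in any arm that loses people. And if the arms lose people at different rates, a difference in retention appears as a difference in morbidity. Reducing morbidity over 6 months is among the aims listed in the Discussion, so the comparison will probably be reported and read.

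**Working it through.** **Inputs from the protocol:** counts over 6 months; independent t-test; 5% alpha; 1:1 allocation; 120 enrolled per arm; 20% expected attrition overall; missing set to 0.

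**Inputs that are assumptions:** dropout by arm (20%/20%, 25%/15% and 30%/10%, each averaging 20%); true event rate (0.1 to 1 event per person per 6 months, equal in both arms); overdispersion (gamma-Poisson, shape 0.5). The plan gives no expected count or power for morbidity, so there is no figure of its own to reproduce.

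**Two readings of the rules.** The article does not say whether a leaver's partial count is used or the whole value is treated as missing, so both are carried through. Let d be the proportion lost.

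- Partial counts kept, losses uniform over follow-up: expected count = true mean × (1 − d/2).
- Leavers set to 0: expected count = true mean × (1 − d).

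**Level.** If all 20% fall under these rules, the recorded mean is 1 − 0.20/2 = 0.90 or 1 − 0.20 = 0.80 of the true mean. The 20% covers the whole protocol (12 weeks plus 6 months), so not all of it need fall in the follow-up window. The 0.80 applies if every leaver, including those lost during the intervention, is imputed as 0. If those lost earlier are left out of the comparison and partial counts are kept, the undercount is below 10%.

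**Ratio of mean counts when the true ratio is 1.00**

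| Dropout | Partial counts kept | Leavers set to 0 |
|---|---|---|
| 20% vs 20% | 0.90/0.90 = 1.00 | 0.80/0.80 = 1.00 |
| 25% vs 15% | 0.875/0.925 = 0.95 | 0.75/0.85 = 0.88 |
| 30% vs 10% | 0.85/0.95 = 0.89 | 0.70/0.90 = 0.78 |

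The ratio is always below 1 for the arm that loses more people.

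**False-positive rate of the t-test.** Simulated with 120 per arm, two-sided 5%, equal true rates, overdispersed counts and 20,000 runs per case. Each range runs over 0.1 to 1 event per person.

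| Dropout | Partial counts kept | Leavers set to 0 |
|---|---|---|
| 20% vs 20% | about 5% | about 5% |
| 25% vs 15% | 5% to 5.5% | 5% to 8% |
| 30% vs 10% | 5.5% to 7.5% | 7% to 17% |

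The result depends on the variance assumed. With plain Poisson counts, leavers set to 0 and 0.2 to 1 event per person, the rates are 7% to 13% at 25% versus 15%, and 11% to 35% at 30% versus 10%.

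**With a time denominator.** In the Poisson simulation with partial counts, events per observed person-time gave rate ratios of 0.999 to 1.002 in every dropout scenario. Dropout was unrelated to event risk in these simulations.

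**The case against.** The strongest objection is that the article does not describe how a leaver enters the comparison. It does not say when entries in the morbidity tool are handed in. If the tool is returned only at the last visit, a leaver has no partial count, only a missing value. This stands, and it is why both readings are shown. It does not remove the problem, because the rule for missing values is zero, which is the less favourable of the two.

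A second objection is that a t-test does not rule out a rate. The same sentence applies it to program adherence, which is defined as a ratio. That is fair: the test alone is not the fault. But morbidity, unlike adherence, is defined by number and given no denominator.

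A third is that the documents do not show unequal dropout. That is correct. A reader might infer that the plan favours the education arm, since that arm carries 18 extra classes and participants know their allocation. The protocol gives no attrition by arm, and both arms follow the same exercise program, so neither the direction nor the existence of a gap is established. A reader might also infer that the t-test is invalid as planned. With equal dropout it keeps its 5% level; only the morbidity level is understated.

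The analysis plan is not shown, but this is not a detail left to it: the protocol already fixes both the test and the imputed value.

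**Conclusion.** The concern holds in conditional form. As written, the rules count unobserved follow-up as event-free. Morbidity is understated whenever participants are lost: by 20% if the full 20% attrition is imputed as zero, and by 10% if all of it falls evenly within follow-up and partial counts are kept. The comparison between arms is distorted only if dropout is unequal. At a 10-point gap the distortion is modest (ratio 0.95 to 0.88). It becomes serious at a 20-point gap (0.89 to 0.78), mainly when leavers are set to zero and events are common. These sizes rest on assumed dropout by arm, event rates and overdispersion. No primary or secondary conclusion depends on this outcome, so the severity is minor.

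**What to change.** 1. In the missing-data section (item 20c), exempt diabetes-related morbidity from replacement by zero.
2. In Statistical methods, Tertiary outcomes, replace the t-test for morbidity with a negative binomial model (or Poisson with robust standard errors) of the event count on arm and centre. Use log(months of follow-up actually reported) as offset, and report the rate ratio with its confidence interval.
3. Record the months covered, either at the monthly calls or from the returned tool. The protocol describes the calls only as reminders, so this has to be written in.
4. Participants with no follow-up time contribute no person-time. Report their number by arm.
5. State that the rate model removes the bias only if dropout is unrelated to event risk.

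The cost is one derived variable, a short addition to what is recorded, and two changed sentences. No extra participants or visits are needed.
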